### Sample size

The sample size calculations provided below were performed following *G*Power* [52]. Since for objective 2b and objectives 3a and 3b (Table 1), no statistical analyses will be carried out, a sample size calculation is not relevant for these objectives.

With regard to objectives 1a and 1c, here, the main study parameter is the CEBA profile, which is latent and thus needs to be derived from performance on neuropsychological tests and questionnaires regarding the CEBA domains. For identification of the CEBA profiles, latent profile analysis will be performed. A minimum sample size of 300 is suggested for latent profile analysis to ensure that there is sufficient power to estimate all model parameters and recover the true number of classes [53, 54]. Therefore, the aim is to include a minimum of 300 patients. For objective 1b, the main study parameters are possible differences between PwMS and HCs on neuropsychological tests and questionnaires regarding symptoms in the different CEBA domains, which will be investigated through the performance of MANOVAs and ANOVAs. A power calculation (with a medium effect size [Cohen’s f] = 0.5, α = 0.05, power = 0.95) results in a minimal sample size of n = 60, which is expected to be exceeded with our goal of including 300 PwMS and 100 HCs for comparison of performance in the CEBA domains. With regard to objective 1d, here, the main study parameters are possible differences in CEBA symptoms between T0 and T1, which are derived from scores on neuropsychological tests and questionnaires regarding the CEBA domains. To investigate the extent to which individual CEBA symptoms are stable over time, repeated measures MANOVAs and ANOVAs will be performed to compare T0 to T1. Within-between interactions will be used. Here, a power calculation using repeated measure analysis (with medium effect size Cohen’s f = 0.5, α = 0.05, and power = 0.95) results in a total sample size of n = 54. Therefore, the aim is to include a minimum of 54 patients for comparing T0 to T1. Since objectives 1e and 1f, as well as objective 2a, depend on the CEBA profiles yet to be identified, the corresponding analyses are considered exploratory, and therefore, no sample size calculation will be provided at this stage. At a later stage, after the CEBA profiles have been identified, sample size calculations for these objectives will be provided, again using *G*Power* [52].

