***(2) Phase 2: To validate CEBA profiles and develop the CEBA screening instrument***	
To achieve these objectives, it will be investigated (2a) whether the identified CEBA profiles can be replicated in a new sample of PwMS. Subsequently, (2b) a feasible screening instrument allowing timely identification of CEBA profiles among PwMS will be developed, in order to indicate the most suitable neuropsychological rehabilitation treatment	

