## Methods

### Study design

The MS-CEBA study is an observational, prospective, cohort study consisting of three phases, as outlined in Table 1. The study aims to include a group of 300 PwMS in Phase 1, of whom 54 will undergo retesting after one year to investigate the stability of the results. Additionally, a group of 100 healthy controls (HCs) will be included in Phase 1. After two years, a second group of 100 PwMS will be included in Phase 2 to investigate whether the results of Phase 1 can be replicated, thereby validating the CEBA profiles. A neuropsychological screening instrument for timely identification of CEBA profiles will then be developed. In Phase 3, a qualitative evaluation of a small group of PwMS (n = 10) from Phase 2 who sought neuropsychological rehabilitation treatment using the advice obtained with the screening instrument (as a part of clinical care, not an intervention in this study) will be performed to identify whether and how this treatment adequately matched their expectations. If necessary, suggestions for adjustments to, or combining of, existing neuropsychological treatments in future research will be made based on this evaluation.

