#### Phase 2: Validation of CEBA profiles and development of the CEBA screening instrument

For Phase 2, a new sample of 100 PwMS will be included following the same procedure for inclusion and assessment as in Phase 1 after approximately two years. Additionally, the development of the CEBA screening instrument will take place. In the event that symptoms in different CEBA domains prevail simultaneously within one CEBA profile, the highest experienced burden of the PwMS in question will be used to help select on which CEBA domain initial neuropsychological rehabilitation treatment should focus. The screening instrument will therefore consist of a concise set of neuropsychological tests and questionnaires identifying combinations of symptoms in the different CEBA domains combined with a short anamnesis regarding the highest experienced burden. Attached will be a manual outlining how to easily derive CEBA profiles from scores on the tests and questionnaires used, along with an advice regarding which neuropsychological rehabilitation treatment would be the most suitable for which combination of CEBA profile and highest experienced burden.

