In 2b), development of the screening instrument, and in **Phase 3: Evaluation of the recommended neuropsychological rehabilitation treatment**, no statistical analysis will be performed. 

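### The plan rules out any statistical analysis for building the screening instrument, so the study as written gives no figure for how well the short form recovers the full-battery profile

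*Protocol article*

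**What the plan says.** Table 1 of the Protocol article sets objective 2b: "a feasible screening instrument allowing timely identification of CEBA profiles among PwMS will be developed", so that the most suitable treatment can be indicated. The Phase 2 procedures describe the product: "The screening instrument will therefore consist of a concise set of neuropsychological tests and questionnaires", together with a short interview on highest burden. They add: "Attached will be a manual outlining how to easily derive CEBA profiles from scores on the tests and questionnaires used". Treatment advice is to be given for each combination of profile and burden.

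On analysis, the Statistical analysis section says of 2b and Phase 3 that "no statistical analysis will be performed". The Sample size section repeats this: "Since for objective 2b and objectives 3a and 3b (Table 1), no statistical analyses will be carried out". It concludes from this that these objectives need no sample size calculation. For objectives 1e, 1f and 2a, by contrast, the same section postpones the sample size calculation to a later stage.

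On timing, the Study design section places development after inclusion of the Phase 2 sample: "A neuropsychological screening instrument for timely identification of CEBA profiles will then be developed". It then describes the Phase 3 participants as people from Phase 2 "who sought neuropsychological rehabilitation treatment using the advice obtained with the screening instrument".

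**The concern.** The profiles are latent. They come from a latent profile analysis of the raw scores on the whole battery (Primary outcome section). A shorter instrument has to reproduce that classification from fewer scores and a simple rule. Expert judgement can guide which tests are practical, but only an analysis can show how often the short form puts a person in the same profile as the full battery.

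This is a positive statement made in two places, not detail left to an analysis plan. The authors separated objectives whose calculation comes later from those that have none, and put 2b in the second group. A separate plan containing such an analysis would contradict this text.

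At stake is the interpretation of the instrument and of what follows from it. The Objectives section foresees referral on the basis of the instrument, and Phase 3 is to judge whether this way of selecting treatment is appropriate. If the misclassification rate is not reported, a poor match between person and treatment may reflect a wrong profile rather than an unsuitable treatment.

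**Working it through.** The documents give no sample size, power or accuracy target for 2b, so there is no figure to reproduce. The check has three parts.

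**1. Does another planned analysis fill the gap?**
- Objective 2a applies the Phase 1 model to the new sample and compares the distribution of membership with Phase 1 by a chi-square test. Similar class shares in two samples do not show that a shorter tool classifies individuals correctly.
- Objective 1f, model 2, uses the most discriminating scores as predictors, but the outcome is societal participation, not profile membership.
- Phase 3 is qualitative, with n = 10, limited to people who sought treatment on the advice, and has no comparison with a reference profile.

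None of these yields agreement, sensitivity or specificity for the instrument.

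**2. Is the order of steps clear?**
- Study design and Table 1 place development after the Phase 2 replication.
- The Phase 2 procedures say only that development takes place in addition to the new sample.
- Study design and the Phase 3 procedures have Phase 2 participants acting on advice from the instrument.

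The documents do not say when the instrument is final relative to the assessment of the people who receive its advice.

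**3. What could the planned sample deliver?**

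Inputs: 100 Phase 2 participants, all with the full battery (Table 2). Assumptions, none of them from the documents: the observed agreement, sensitivity and specificity, and the profile shares. The formula is the Wilson 95% interval, with z = 1.96:

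(p + z²/2n ± z·√[p(1−p)/n + z²/4n²]) / (1 + z²/n)

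Worked example, overall agreement 80/100:
- centre = (0.80 + 0.0192)/1.0384 = 0.789
- half-width = 1.96 × √(0.0016 + 0.000096)/1.0384 = 0.078
- interval = 71 to 87%

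Other overall agreement:
- 70/100: 60 to 78%
- 90/100: 83 to 94%

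Sensitivity for one profile, by assumed share:
- 10% (10 people), 8/10 = 80%: 49 to 94%
- 20% (20 people), 16/20 = 80%: 58 to 92%
- 25% (25 people), 20/25 = 80%: 61 to 91%
- 33% (33 people), 26/33 = 79%: 62 to 89%

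Specificity at a 20% share (80 people without the profile), 68/80 = 85%: 76 to 91%.

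These intervals treat the full-battery profile as known and apply to raw agreement. The interval for kappa also depends on the profile shares.

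**The case against.** The strongest reply is that nothing is lost for good. Both PwMS samples take the full battery, so an agreement table could be made later. Each Phase 3 participant comes from Phase 2, so that person's full-battery profile can be looked up. This stands, and it limits the harm: the defect lies in what the plan commits to, not in the data. The plan still says that the analysis will not be done.

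Three stronger readings are tempting, and the documents do not support them.
- A reader might infer that no independent sample remains to test the instrument. No section says that Phase 2 data will be used to choose tests or rules. If the instrument is built from Phase 1, Phase 2 is independent. Only the unclear timing is established.
- A reader might take the instrument to be the study's main outcome. The primary outcome is the profiles, the instrument is not among the secondary outcomes, and its development depends on profiles being found and validated.
- A reader might infer that an untested tool will go into general use when the study ends. Routine use appears only in the Discussion, as a future benefit. Within the study, the advice feeds into ordinary clinical care and also depends on highest burden.

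**Conclusion.** The point holds. The plan excludes statistical analysis for an objective that cannot be met without it, and no other planned analysis supplies the missing result. Followed as written, the study would report no figure for how well the short form recovers the full-battery profile. The primary and secondary outcomes are not affected.

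The size of any misclassification cannot be derived from the documents. What can be stated is the precision that the existing Phase 2 sample would allow: about 6 to 9 points either side for overall agreement between 90% and 70%, but an interval 45 points wide for a sensitivity of 80% in a profile with an assumed 10% share, and 30 points wide at 25%. The sample supports a useful overall figure and only rough per-profile figures.

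Separately, the statements on when the instrument is developed and when Phase 2 participants act on its advice must be reconciled.

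**What to change.** 1. Remove the statement that 2b has no statistical analysis from both the Statistical analysis and the Sample size sections, and replace the dismissal of a sample size with the expected precision.
2. Derive the test subset and scoring rule from Phase 1 data only (n = 300), with internal cross-validation. The selection method is open; penalised multinomial regression and stepwise removal of indicators are two options.
3. Fix the instrument before it is applied to Phase 2 data. Then score it in the 100 Phase 2 participants from their full battery.
4. Report overall agreement (for example kappa) and per-profile sensitivity and specificity against the full-battery profile, with 95% CIs. Allow for uncertain class membership, for example by using posterior probabilities, as the plan already does in its three-step analysis for 1e.
5. Reconcile Study design, the Phase 2 procedures and the Phase 3 procedures, so that it is clear when the instrument is final and which version the advice to Phase 2 participants comes from.

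The cost is analyst time and protocol wording, without new assessments. When the article was written, 167 people had taken part, fewer than the 300 PwMS planned for Phase 1 alone, and recruitment was to run to the end of 2026, so the change was still possible then. Three downsides should be stated. Derivation has to come before the analysis of Phase 2 data. Per-profile intervals will be wide. Agreement will be somewhat optimistic, because the short form and the reference share the same test scores from the same session.

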## Results

Recruitment started in mid-2023 and is planned to continue until the end of 2026. Currently, 167 participants have participated in the study. The first publications are expected in early 2026.

## Discussion

To the best of our knowledge, the MS-CEBA study is the first to investigate, over the whole spectrum of CEBA domains, whether there are symptoms in the different domains that consistently occur together in PwMS. In other words, if certain CEBA profiles can be identified, and in turn, how these possible profiles are related to the level of societal participation of PwMS. We believe that increased awareness of and knowledge on the combinations of neuropsychological problems in MS is a meaningful contribution to the literature and to neuropsychological rehabilitation care for PwMS for various reasons.

First, if specific CEBA profiles are indeed discovered, this is an important step in systematically mapping the neuropsychological symptoms that this heterogeneous patient group presents with. This allows for a more structured screening of these combinations of neuropsychological symptoms in PwMS by developing a time-efficient screening instrument taking into account all CEBA domains as well as the highest experienced burden. Standard deployment of the screening instrument in clinical practice, and thereby more consistent and timely attention to the combinations of neuropsychological symptoms of MS, will help prevent these combinations of symptoms from going unnoticed for an extended period of time. Therefore, in the future, PwMS who present with a given CEBA profile will be more timely and fully informed about the most suitable existing neuropsychological rehabilitation treatment options for their profile, and if desired, treatment can be started in a timely manner.

Second, the current dataset will enable the exploration of demographic and medical data as potential predictors for specific CEBA profiles and, additionally, how each corresponding CEBA profile relates to the level of societal participation. This provides insight into potential risk factors for certain CEBA profiles and the corresponding level of societal participation, contributing further to the timely identification of CEBA profiles and, associated with this, the timely indication for neuropsychological rehabilitation treatment in PwMS.

Third, identifying CEBA profiles and patients’ highest experienced burden when different domains prevail in a profile allows us to examine whether the existing neuropsychological rehabilitation treatment options, currently all targeting a single CEBA domain, adequately address the needs of PwMS with a certain CEBA profile. If, based on the qualitative evaluation in the current study, it turns out that (part of) the existing treatments do not sufficiently align, this serves as a crucial foundation for further research exploring potential adjustments to these existing treatments.

## Conclusions

In conclusion, the results of the MS-CEBA study will contribute to a more comprehensive understanding of the entire spectrum of neuropsychological symptoms in MS and will enable timely recognition of combinations of symptoms in the different CEBA domains (that is, CEBA profiles) in PwMS in clinical practice. This, to ensure that PwMS can be referred to the treatment option most suitable for a given CEBA profile if needed. All of this, with the ultimate aim of maintaining or improving societal participation, and thereby quality of life, of PwMS to the best of our ability.

## Data Availability

Depending on the type of data and the associated privacy regulations, data from the MS-CEBA study will be made available upon reasonable request to the principal investigator ([name]).

## Abbreviations

CEBA: Cognitive, Energetic, Behavioural, Affective
CCMO: Dutch Central Committee on Research Involving Human Subjects
eCRF: Electronic Case Report Form
EDSS: Expanded Disability Status Scale
HCs: Healthy Controls
IPA: Impact on Participation and Autonomy Questionnaire
MCL: Medical Centre Leeuwarden
MHG: Martini Hospital Groningen
MREC: Medical Research Ethics Committee
MS: Multiple Sclerosis
NPA: Neuropsychological Assessment
PwMS: People with Multiple Sclerosis
REDCap: Research Electronic Data Capture
SPSS: Statistical Package for the Social Sciences
UMCG: University Medical Centre Groningen
